#### Descriptive analyses at baseline

Descriptive statistics of demographic and potential confounding variables will be presented at baseline for the purposes of investigating the comparability of the intervention groups, and to provide descriptive information about the study sample. Potential confounding variables will include those presented in Figure 2, practitioners' self report of the average number of patients they treat per week, and the average number of acute LBP patients they treat per week (collected in the practitioner baseline questionnaire). In addition, we will compare between groups measures of the patients' pain (assessed by both the practitioner and patient) and general health (assessed by the practitioner) collected at the first visit of incident cases of acute LBP over the data collection period.

**Figure 2 F2:**
[figure not shown]
**Potential confounding variables adjusted for in the primary analyses**. ^1^Practitioner checklist; ^2^Exposure period is the number of data collection days post-patient entry into the trial. ^3^Clinical file audit; ^4^Practitioner questionnaire; ^5^Stratification variable; ^6^Imaging referral excluding x-ray; ^7 ^Adjusted for the baseline of the relevant behavioural construct (*e.g*., knowledge (Table 2)) for the specified behaviour (managing patients without referral for plain x-ray or advising patients to stay active); ^8^Practitioners answer yes to the question 'Do you primarily treat Work Cover (compensable) patients at your main practice?'; ^9^Patient questionnaire; ^10^Managing patients without referral for plain x-ray; ^11^Advising patients to stay active; *[100]; ^†^[100,101]; ^±^[102]; ^‡^[103]; ^·^[104]; ^II ^[76]; ^¶^[105]; °[106].

#### Primary analyses

We will estimate the effectiveness of the intervention on primary and secondary outcomes with marginal modelling using generalised estimating equations (GEEs). These models will appropriately account for correlation of responses within practice. We plan to fit an exchangeable correlation structure, where responses from the same practice are assumed to be equally correlated [50,72]. Additionally, we intend to use robust variance estimation that will provide valid standard errors even if the within-cluster correlation structure has been incorrectly specified [73,74]. For binary outcomes, a logit link function will be used. In the event that the ICC of an outcome for a particular analysis is negative, we will fit a generalised linear model with no adjustment for clustering (*e.g*., ordinary linear regression), making the assumption that in the context of cluster-based evaluations, negative ICCs are more likely to occur through sampling error than because of a true negative ICC [50].

Our primary analyses of outcomes will include adjustment for stratification variables (professional group and location of the practice) and pre-specified potential confounding variables (Figure 2). The potential confounders have been selected through discussion amongst the investigators and from published research (see Figure 2 notes). All pre-specified confounders will be included in the models even when no baseline imbalance exists. We have chosen this approach because confounder selection strategies that are based on collected data, (*e.g*., selecting confounders using preliminary statistical tests) result in models with poor statistical properties, such as incorrect type I error rates [75-78]. In the circumstance that there is limited data or events (*e.g*., advised bed rest), or both, to adjust for all confounders, we will report estimates of intervention effect from models including only the stratification variables, and baseline of the outcome variables where appropriate (FAB, intention, and behavioural constructs).

Estimates of intervention effect from these models with binary outcomes will yield odds ratios. In addition to the odds ratios, we plan to also provide estimates of risk difference to aid interpretability and provide greater information to fully assess the implications of the intervention effects [79]. Estimates of risk difference will be estimated from GEEs, with robust variance estimation, using an identity link function [80]. For each outcome, the estimate of intervention effect and its 95% CI will be provided. For the primary outcomes, we plan to provide estimates of ICCs and their 95% CIs.

Regression diagnostics will be used to assess the influence of outliers on estimates of intervention effect and for analysing residuals. No adjustment will be made for multiple testing. All tests will be two-sided and carried out at the 5% level of significance.

#### Secondary analyses

We will conduct a subgroup analysis to examine whether the effect of the intervention on x-ray referral is modified by professional group (physiotherapist versus chiropractor). We hypothesise that the effect of the intervention may differ by professional group because x-rays are seen as more integral to the treatment of patients for chiropractors compared with physiotherapists [22]. We will examine this by fitting a model that includes an interaction term between intervention group and professional group. The estimated ratio of odds ratios and its 95% CI will be presented from this model.

GEEs will yield unbiased estimates of intervention effect only when data are missing completely at random, or when known covariates that are associated with the missing data mechanism are included in the model (missing at random) [69]. As part of the secondary analyses, we plan to identify potential predictors of missing data through modelling (*e.g*., [81]), and include these predictors in the primary analysis model. We will investigate methods to impute missing outcome data collected at baseline (*e.g*., baseline behavioural constructs, FAB) [82]. Finally, we will investigate methods to adjust for potential differential recruitment [68].

A disadvantage of using GEEs is that only one level of clustering can be modelled. For data collected at the patient level, there are three levels of data: practices, practitioners, and patients. It is possible to allow for clustering at the practice level or the practitioner level. While we have chosen to adjust for clustering at the practice level, because this is the unit of randomisation, there may be an argument for adjusting at the practitioner level if the variation at this level is larger; this could be predicted to arise because the practitioner has a more direct influence on patient outcomes (such as x-ray referral). We will therefore undertake sensitivity analyses investigating the impact of allowing for clustering at the level of the practitioner.

We plan to undertake explanatory analyses to investigate if intervention effects are mediated by our hypothesised predictors of practitioner behaviour [83-85]. Detailed description of our theoretical model and results of these explanatory analyses will form separate publications.

Finally, we plan to undertake analyses comparing the outcomes (*e.g*., 'x-ray referral,' 'imaging referral excluding x-ray') measured via different methods of data collection (practitioner completed checklists, patient completed checklists, file audit). In addition, we will undertake statistical analyses comparing proxy (*e.g*., clinical decisions in response to vignettes) and direct methods of measuring clinical behaviour [86]. These analyses will be undertaken to add to our knowledge about the design of future trials, but will not be considered part of the trial effectiveness analyses, and will inform a separate publication.

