### Trial objectives

The primary objective of the ALIGN trial is to estimate the effectiveness of a theory-based intervention that aims to increase physiotherapists' and chiropractors' (in Victoria, Australia) compliance with a CPG for acute LBP, compared with providing practitioners with a printed copy of the guideline. Specifically, our primary objectives are to establish if the intervention is effective in:

(i) Reducing the percentage of acute non-specific LBP patients who are either referred for an x-ray, or receive an x-ray (practitioner behaviour);

(ii) Improving the mean level of disability for patients three months post-onset of an episode of acute non-specific LBP (patient level health outcome).

Secondary objectives include estimating the effects of the intervention for secondary outcomes in the following categories: (i) practitioner behaviour (provided advice to stay active, advised bed rest, referred for imaging excluding x-ray), (ii) predictors of practitioner behaviour (practitioner intention to behave in a manner consistent with the CPG's recommendations, behavioural constructs (*e.g.*, knowledge, beliefs about capabilities)), (iii) patient health outcomes (pain severity, health-related quality of life (HRQoL)), (iv) patient health behaviour (x-ray occurred), and a (v) predictor of patient health behaviour (patients' fear-avoidance beliefs (FAB)). In addition, we will assess cost-effectiveness based on the practitioner and patient-level outcomes described above, as well as assessment of HRQoL, health service utilisation, and productivity gains/losses.

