### Sample size

The primary practitioner outcome is x-ray referral. In our original sample size calculation for this outcome, we estimated that we would require 136 practices (68 physiotherapy and 68 chiropractic practices), each completing checklists for an average of 20 patient participants (providing a total of 2,720 patient participants), to provide 80% power to detect a difference of 10% in x-ray referral between intervention groups. This assumed a 39% x-ray referral rate in the control group, a 5% significance level, and an ICC of 0.10, and allowed for 20% attrition in practices. Empirical research has suggested ICCs of the order of 0.10 for process variables, such as x-ray referral, in primary care [63]. Data on x-ray referral rates were not available for the Australian context, so the x-ray referral rate of 39% was estimated from international research and assumptions regarding the process of x-ray referral in Australia. More specifically, for chiropractors, several international studies have estimated that referral for x-ray for acute LBP ranges from 62% to 72% [17,20,23]. For physiotherapists, we assumed that x-ray referral rates would be similar to those found in Australian general practice, which has been estimated at 28% [64], because many physiotherapists treat patients with LBP on referral from, and in conjunction with, GPs. Because we intended to recruit an equal number of patient participants from physiotherapy and chiropractic practices, we estimated the pooled x-ray referral rate to be 47%. Interventions comparing standard CPG dissemination with no intervention control groups have shown improvements in care of approximately 8% [4]. We therefore anticipated a decrease in the percentage of x-ray referral in the control group of this magnitude, providing an estimated referral rate of 39%.

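### The professional-group subgroup result is specified only as a ratio of odds ratios, so it will not show whether the percentage-point reduction in x-ray referral differs between physiotherapists and chiropractors

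*Protocol article*

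**What the plan says.** Secondary analyses plans a subgroup analysis of x-ray referral by professional group: "We will examine this by fitting a model that includes an interaction term between intervention group and professional group". The stated output is: "The estimated ratio of odds ratios and its 95% CI will be presented from this model". No other interaction measure is named.

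The scale follows from Primary analyses, which fixes the link: "For binary outcomes, a logit link function will be used". The same section then adds a second scale for the intervention effects: "In addition to the odds ratios, we plan to also provide estimates of risk difference to aid interpretability". Those risk differences come from GEEs with an identity link and robust variances. They are described for the effect on each outcome, not for the interaction.

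Elsewhere the effect is framed in percentages. The first objective under Trial objectives is a reduction in the percentage of patients referred for or receiving an x-ray. The original sample size was chosen "to provide 80% power to detect a difference of 10% in x-ray referral between intervention groups". Expected precision with 168 practices is given first as ±5% to ±7% on the risk difference. The economic evaluation reports cost per x-ray avoided.

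The Sample size section takes 28% referral for physiotherapists and 62% to 72% for chiropractors, pools these to 47%, and subtracts 8 points for guideline dissemination to reach 39% in the control group. It gives no control rate by profession.

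**The concern.** The subgroup question is whether the intervention works differently in the two professions. The answer depends on the scale when baseline rates differ, and here they differ greatly. The null hypothesis of the planned test is equal odds ratios. A reader who thinks in x-rays avoided per 100 patients, as the objective and the economic evaluation do, wants to know whether the percentage-point reductions are equal. The planned output does not answer that.

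Two readings could go wrong. If the intervention removes the same number of x-rays per 100 patients in each profession, the ratio of odds ratios can still differ from 1 and be read as a smaller benefit among chiropractors. If the odds ratio is the same in both professions, the result reads as no difference, although chiropractic practices avoid more x-rays per 100 patients. Decisions about where to use the programme could rest on either reading.

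**Working it through.** **The plan's own figure.** For 39% versus 29%, two-sided 5% and 80% power with continuity correction, 371 patients per arm are needed. The design effect is 1 + (20 − 1) × 0.10 = 2.9. Then 371 × 2.9 / 20 = 53.8, so 54 practices per arm and 108 in all, and 108 / 0.8 = 135, against 136 stated. The stated inputs are therefore understood correctly.

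**Inputs.** 133 physiotherapy and 77 chiropractic practices, 20% attrition (168 remain), 1:1 allocation, 20 patients per practice, ICC 0.10. Effective patients per arm:
- physiotherapy: 133 × 0.8 / 2 × 20 / 2.9 = 367
- chiropractic: 77 × 0.8 / 2 × 20 / 2.9 = 212

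**Control rates by profession (assumptions).** The 8-point drop is applied in the article only to the pooled rate, so three versions are used:
- no drop: 28% and 67% (the middle of 62% to 72%)
- proportional drop: 28 × 39/47 ≈ 23%, and 66 × 39/47 ≈ 55%, where 66% is the chiropractic rate implied by the pooled 47%
- 8 points off each: 20% and 59%

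**Equal 10-point reduction in both professions.** With OR = [p₁/(1 − p₁)] / [p₀/(1 − p₀)], the ratio of odds ratios (ROR) is the chiropractic OR over the physiotherapy OR. SE(log ROR) = √Σ 1/[n p(1 − p)] over the four cells. The chance of significance comes from a two-sided 5% Wald test.

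At 20%/59%:
- physiotherapy OR = (0.10/0.90)/(0.20/0.80) = 0.444
- chiropractic OR = (0.49/0.51)/(0.59/0.41) = 0.668
- ROR = 0.668/0.444 = 1.50, log ROR = 0.407
- SE = √(0.0170 + 0.0303 + 0.0195 + 0.0188) = 0.293
- z = 0.407/0.293 = 1.39, so the test is significant in about 28% of trials

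| Control rates | ORs (physio, chiro) | ROR | SE(log ROR) | Significant |
|---|---|---|---|---|
| 28% / 67% | 0.564, 0.653 | 1.16 | 0.269 | about 8% |
| 23% / 55% | 0.500, 0.669 | 1.34 | 0.278 | about 18% |
| 20% / 59% | 0.444, 0.668 | 1.50 | 0.293 | about 28% |

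In every row the difference in risk differences is zero. The result is driven by how low the physiotherapy rate is. At 20%/59%, an equal 5-point fall gives an ROR of 1.16 and significance in about 8% of trials.

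**The converse: a common odds ratio.** The planned overall effect is OR = (0.29/0.71)/(0.39/0.61) = 0.64. Applied to both professions at 20%/59%, it lowers 20% to 13.8% (6.2 points) and 59% to 47.9% (11.1 points). The ROR is exactly 1. The difference in risk differences is 11.1 − 6.2 = 4.9 points. A test of that difference would be significant in about 14% of trials, against 5% for the ROR.

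**Precision on the additive scale.** At 20%/59% with equal 10-point falls, the SE of the difference in risk differences is 0.0547, so the 95% CI half-width is 1.96 × 0.0547 = 10.7 points.

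These approximations ignore covariate adjustment and variation in cluster size, and use one ICC for both professions.

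**The case against.** The planned test is sound on its own terms. The logit link is fixed for binary outcomes, the odds ratio is the measure it yields, and the ratio of odds ratios is the matching interaction measure. A reader might infer from the 28% that the test has an inflated false-positive rate. It does not: odds ratios of 0.44 and 0.67 really differ, so those rejections are power against a true difference on the odds scale. A fall from 20% to 10% halves referral, while one from 59% to 49% cuts it by about a sixth, so saying chiropractors changed proportionally less would be a fair description. This stands.

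The article does not exclude further displays, and it sets no rule for declaring that the programme works less well in one profession. A reader might infer that such a claim will be made, but the document does not say so. It is also true that no control rates by profession are given; under a proportional drop or no drop the distortion is much smaller.

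A reader might also infer that the planned test gives up a great deal of power for absolute differences. That would need an effect well beyond the planned one: near the planned odds ratio of 0.64 the gap is only about 10 points. Nor would it help to let the risk-difference interaction alone decide, because it has the mirror-image property: it departs from zero whenever a common odds ratio meets different control rates.

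What remains is narrower. The article specifies an output for this analysis, and that output leaves out the scale on which it states its objective and powered effect. The planned risk differences are for main effects and are not carried into the subgroup, where baseline rates differ most.

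**Conclusion.** The point holds as a matter of interpretation and not as an error in the test. The ratio of odds ratios is valid, but alone it does not show whether the percentage-point reduction differs between professions. Under an equal 10-point fall it takes values of about 1.16 to 1.50 and is significant in about 8% to 28% of trials. Under a common odds ratio near the planned 0.64 it hides reductions of about 6 and 11 points at 20%/59%. These figures rest on assumed control rates by profession, 168 practices, 20 patients per practice and an ICC of 0.10. The primary results, the sample size and the economic evaluation do not use this interaction and are unaffected. It is a cheap improvement worth making before outcomes are analysed.

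**What to change.** In Secondary analyses, also fit the intervention-by-profession interaction in the identity-link GEE already planned under Primary analyses. If that model does not converge, obtain the risk differences by standardisation from the logit GEE. Report the difference in risk differences with its 95% CI beside the ratio of odds ratios, and give referral percentages and risk differences for each profession. Require that any statement that the professions respond differently, or alike, names the scale. Do not make either scale the sole decision rule.

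The cost is a sentence or two of analysis text and one extra term in a model already planned; no new data or patients are needed. The downside is that two interaction estimates must be read together, and the additive one will be imprecise (half-width about 11 points under the assumptions above), so it should be presented as an estimate with its interval.

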We initially intended to recruit 136 practices (68 physiotherapy and 68 chiropractic practices), but received a better than expected response with 210 practices wishing to participate. This included 133 physiotherapy practices with 180 physiotherapists, and 77 chiropractic practices with 88 chiropractors. Given the uncertainty in the parameters informing our sample size calculation (*e.g*., intra-cluster correlation coefficient (ICC), see 'Sample size' section), we made a decision to include all practices.

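### The practitioner-clustered sensitivity analysis sits below the unit of randomisation; if colleagues in a practice are positively correlated, its standard errors are modestly too small

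*Protocol article*

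**What the plan says.** The Primary analyses section describes marginal models fitted by GEE with practice as the cluster: "We plan to fit an exchangeable correlation structure, where responses from the same practice are assumed to be equally correlated". It adds "robust variance estimation that will provide valid standard errors even if the within-cluster correlation structure has been incorrectly specified".

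The Secondary analyses section returns to the choice of level. It notes that "For data collected at the patient level, there are three levels of data: practices, practitioners, and patients" and that "A disadvantage of using GEEs is that only one level of clustering can be modelled". It defends the primary choice: "While we have chosen to adjust for clustering at the practice level, because this is the unit of randomisation". It then says "there may be an argument for adjusting at the practitioner level if the variation at this level is larger", on the ground that practitioners influence outcomes such as x-ray referral more directly, and concludes: "We will therefore undertake sensitivity analyses investigating the impact of allowing for clustering at the level of the practitioner".

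On numbers, the recruitment section reports "133 physiotherapy practices with 180 physiotherapists, and 77 chiropractic practices with 88 chiropractors".

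**The concern.** Every practitioner in a practice has the same allocation. For the variance of the intervention effect, the independent units are therefore the practices. A robust variance summed over practitioners omits the covariance between colleagues in one practice. Where that covariance is positive, the variance is understated. Robust estimation does not repair this, because it protects only against misspecified correlation inside whatever is declared to be the cluster.

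The reason given for the analysis does not hold on the protocol's own terms. With practice as the cluster, practitioner-level correlation is part of the within-cluster structure, and the Primary analyses section says the robust variance remains valid when that structure is misspecified. Larger practitioner variation affects efficiency and the choice of working correlation. It gives no reason to move the variance below the randomised unit.

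What is at stake is how the sensitivity analysis will be read. With positive correlation it tends to produce a narrower interval than it should, so it may appear to strengthen the primary result. Any change in the interval would mix a different working correlation with the loss of practice-level correlation, and the two could not be told apart. All tests are at the two-sided 5% level without multiplicity adjustment, so a p-value that crosses 0.05 only in this analysis could be an artefact.

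**Working it through.** **The plan's own figure.** The Sample size section gives 136 practices for 39% versus 29% x-ray referral, 80% power, two-sided 5%, 20 patients per practice, an ICC of 0.10 and 20% attrition. Two proportions with continuity correction need 371 per arm. The design effect is 1 + 19 × 0.10 = 2.9. Then 2 × 371 × 2.9 / 20 = 107.6 practices, and 107.6 / 0.8 = 134.5, close to 136. So the plan itself applies its ICC of 0.10 at practice level.

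**Inputs from the protocol.**
- Practices: 133 + 77 = 210. Practitioners: 180 + 88 = 268. Mean 268 / 210 = 1.28 per practice.
- If each practice has at least one practitioner, at least 2 × 210 − 268 = 152 have exactly one. At most 58 have more than one.
- Patients: 20 per practice × 210 / 268 ≈ 16 per practitioner.

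**Assumptions, not in the protocol.**
- Within-practitioner ICC r_w = 0.10. This borrows the protocol's practice-level value.
- ICC between practitioners of the same practice, r_b = 0.02, 0.05 or 0.10.
- 79%, 15.5%, 4.5% and 1% of practices with 1, 2, 3 and 4 practitioners (mean 1.275).

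**Formula.** For a practice with j practitioners and m patients each, the true variance of the practice total is proportional to A + B, where A = j·m·[1 + (m − 1)·r_w] and B = j(j − 1)·m²·r_b. Clustering on practitioner keeps A and omits B. The ratio of reported to true SE is √[ΣA / Σ(A + B)]. The actual type I error is 2·[1 − Φ(1.96 × ratio)].

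**Main case, m = 16, average per practice.** A = 1.275 × 16 × (1 + 15 × 0.10) = 51.0. The mean of j(j − 1) is 0.155 × 2 + 0.045 × 6 + 0.01 × 12 = 0.70, so B = 0.70 × 256 × r_b = 179.2 × r_b.

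| r_b | B | SE ratio | SE too small by | Type I error |
|---|---|---|---|---|
| 0.02 | 3.58 | 0.967 | 3% | 5.8% |
| 0.05 | 8.96 | 0.922 | 8% | 7.1% |
| 0.10 | 17.92 | 0.860 | 14% | 9.2% |

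At r_b = 0, B = 0 and nothing is understated. The r_b = 0.10 row puts all the correlation at practice level and leaves no practitioner variance. If practitioner variation is the larger share of 0.10, as the protocol's rationale supposes, r_b lies below 0.05.

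**Other splits with the same totals, r_w = 0.10.**

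| Split of the 210 practices | r_b | Ratio, 16 patients per practitioner | Ratio, 20 patients per practice in total |
|---|---|---|---|
| 152 with one, 58 with two | 0.02 | 0.973 | 0.990 |
| | 0.05 | 0.937 | 0.975 |
| 170 / 27 / 8 / 5 with one to four | 0.02 | 0.963 | 0.992 |
| | 0.05 | 0.915 | 0.981 |
| 190 with one, 2 with three, 18 with four | 0.02 | 0.950 | 0.995 |
| | 0.05 | 0.887 | 0.987 |

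The low end of the range comes from the right-hand column. For 152/58 at r_b = 0.02, A = 152 × 20 × 2.9 + 58 × 20 × 1.9 = 11,020 and B = 58 × 2 × 100 × 0.02 = 232. The ratio is √(11,020 / 11,252) = 0.990 and the type I error 5.2%. The last split is deliberately concentrated. It shows that the result depends on an unreported distribution: at r_b = 0.05 the type I error there is 8.2% with 16 patients per practitioner and 5.3% with 20 per practice.

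**Simulation check.** Logistic GEE, exchangeable correlation, robust variance, no intervention effect, 168 practices (the number left after 20% attrition) with 136/22/6/4 having one to four practitioners, about 15 patients each, 300 runs per scenario.

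| Variance on the logit scale | Cluster | Mean SE | Empirical SD | Type I error |
|---|---|---|---|---|
| Half practice, half practitioner | practitioner | 0.106 | 0.117 | 7.7% |
| | practice | 0.113 | 0.114 | 5.0% |
| All at practice level | practitioner | 0.106 | 0.125 | 10.0% |
| | practice | 0.116 | 0.117 | 4.0% |

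With 300 runs the Monte Carlo error is about 1 to 2 percentage points, so this supports the direction and rough size only.

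**The case against.** The strongest reply is that nothing important depends on this analysis. The primary analysis clusters on practice for the right reason, the practitioner-level version is introduced tentatively, and no decision rule or sample size rests on it. That stands, and it is why the point is minor.

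Three further limits also stand. First, the understatement requires positive correlation between colleagues, and the protocol gives no figure for it. The Trial design section expects diffusion between practitioners within intervention practices, which makes a positive value plausible but does not establish it. Second, most practices have one consenting practitioner and contribute nothing to the problem. Third, misspecified clustering leaves the GEE point estimate consistent, so a shift in the odds ratio under practitioner-level weighting is still informative. Only the standard error, interval and p-value are in doubt.

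Holding 20 patients per practice fixed gives milder figures. It is a fair lower case, although each practitioner completes checklists for their own consultations, so patient numbers would be expected to rise with the number of practitioners.

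A reader might infer that the trial's main inference ignores the randomised unit, or that the practitioner-clustered result could replace the primary one. The protocol supports neither reading.

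**Conclusion.** The concern holds in conditional form. As written, the sensitivity analysis clusters below the randomised unit, and its rationale is already met by practice-level robust variance. If colleagues' outcomes correlate positively, the standard error is about 1 to 8% too small and the type I error about 5.2 to 7.1%. This range assumes a within-practitioner ICC of 0.10, a between-practitioner ICC of 0.02 to 0.05 and the main or paired split. With all the correlation at practice level the main split gives about 14% and 9.2%; that is a limiting case which contradicts the protocol's own premise of larger practitioner variation. A more concentrated split of practitioners would raise these figures, and a fixed number of patients per practice would lower them. The calculation uses the ICC assumed for x-ray referral, so it does not size the effect for disability. Severity is minor.

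**What to change.** Reword the sensitivity analysis so that the working correlation reflects practitioners, for example nested within practice, while the robust variance stays clustered on practice. This still addresses the authors' question about where the variation lies and keeps both the marginal odds ratio and valid standard errors.

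A three-level mixed model (patient, practitioner, practice) is optional. For x-ray referral its odds ratio is cluster-specific and must be labelled so, since it is not the marginal quantity of the primary analysis. At most 58 of the 210 practices, before attrition, can separate practice from practitioner variance, so the two ICCs may be imprecise.

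The cost is a sentence of plan wording and a modest programming change. Data collection, sample size and the primary analysis do not change.
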